### Hypotheses

2.2

1.The heritability of response to training will differ according to whether cross-sectional or training data are assessed.2.Response to exercise will be modality specific for each outcome measure.3.Concordance between response to END and RES modes of training will differ between individuals.4.Concordance between twins in a pair in terms of the response to END or RES modes of training will differ between MZ and DZ pairs.

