### Participant recruitment

2.3

Healthy, same-sex DZ and MZ twin pairs, between the ages of 16–40yrs, were recruited to participate in the study. Recruitment started in September 2016 and was facilitated by Twins Research Australia (formerly Australian Twin Registry [33]). Twin pairs in the Metropolitan Perth-based region were sent emails, newsletters and conventional mail regarding participation in the study. Other recruitment methods included advertising in local and Perth-based newspapers, online and social media recruiting, The University of Western Australia (UWA) email lists, flyers around UWA and nearby establishments, and word of mouth. Baseline demographic data is displayed in Table 1, and a participant flow chart in Fig. 1.

**Table 1 tbl1:** Baseline characteristics of participants enrolled in the study.

		Monozygotic (MZ)	Dizygotic (DZ)
		n = 62 (31 twin pairs, 18 F, 13 M)	n = 28 (14 twin pairs, 10 F, 4 M)
		Mean (SD)	Mean (SD)
Age (yrs)	F	24.2 (5.0)	23.8 (4.2)
	M	28.0 (5.9)	22.9 (5.3)
	Total	26.2 (6.1)	23.5 (4.5)
Height (cm)	F	170.2 (4.0)	168.6 (5.9)
	M	180.8 (4.5)	178.0 (6.6)
	Total	174.5 (6.5)	171.8 (7.5)
Weight (kg)	F	67.0 (19.6)	59.3 (9.4)
	M	81.0 (12.8)	69.1 (11.3)
	Total	74.9 (18.9)	62.6 (10.9)
BMI (kg/m^2^)	F	23.0 (6.1)	20.9 (2.8)
	M	24.7 (3.6)	21.7 (2.7)
	Total	24.4 (5.3)	21.1 (2.9)

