The primary objective of the current study is to estimate the MZ and DZ correlations and the variance components A, C and E for each outcome measure cross-sectionally, and in response to exercise training (END and RES). In STATA mixed models effects will calculate intraclass correlation coefficients (r) for MZ and DZ twin pairs. Covariates to be adjusted for (e.g. sex, fat-free mass, VO_2max_, baseline data) will depend on the primary outcome measure. The subsequent rMZ and rDZ, and their respective P-values and 95% confidence intervals will be presented. Differences between intraclass correlations (rMZ vs rDZ) will be assessed using the likelihood-ratio test in STATA to compare mixed effects models constraining covariances for MZ and DZ pairs to be equal with models allowing different covariances for MZ and DZ pairs [69]. If the model allowing different MZ and DZ covariances are significantly better, and rMZ are significantly different to rDZ, A, C and E will then be calculated from the estimates of the DZ covariance and the additional MZ covariance, and confidence intervals for A, C and E will be estimated using the delta method. When rMZ and rDZ are not significantly different then a single model that includes all twin pairs but constrains the covariance to be equal for MZ and DZ pairs will be used in STATA to calculate C and E components only, and their respective 95% confidence intervals. An additional model which estimates covariance for MZ twins but fixes the DZ covariance to be zero will test if the estimated correlations suggest that the equal environments assumption has been violated.

Secondary objectives of this study will be addressed using the individual change with training (END and RES) results for each outcome measure. Response rates for each modality can be derived as a percentage of positive responses (>0) and compared against one another by a Z-test. Concordances can be derived as the percentage of individuals who positively respond to both exercise training modalities (Supplementary Fig. 5). In a similar way to the correlation analyses, within-twin pair concordances for MZ and DZ can be derived for each exercise intervention and compared to each other.

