### Sample size and power

3.2

Power analysis is based on our primary outcome measures which are highly specialized and sensitive; vascular function (FMD), cardiac and cerebrovascular adaptation. Our cardiac publications [6,8,9] have reported significant effects in fewer subjects (n = 10 and n = 13 per group) than we recruited in the present study; we observed highly significant differences utilising highly sensitive MRI. Regarding cerebral measures, previous publications and our pilot work demonstrate that cerebral blood flow is increased in older individuals (n = 9, 65–78 yrs) by 10% after intervention. Our previous twin study publications in a paediatric population [24,31] cross-sectionally revealed FMD correlations of 0.6 and 0.38 in MZ and DZ twin pairs, respectively, in a smaller sample size of 22 (11 pairs) per group [24]. In addition, this study applied an exercise intervention (8 weeks) shorter than the current study (12 weeks), and produced correlations of 0.74 and 0.37 for FMD responses in MZ and DZ groups (n = 24–6 pairs per group) [31]. A power analysis (G*Power v3.1.2), performed using the predicted correlations for rMZ = 0.80 and rDZ = 0.30, assuming alpha = 0.05, indicates that a sample size of 23 individuals in each group provides 80% power.

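### The MZ v DZ comparison of raw within-pair response concordance (hypothesis 4) mixes twin resemblance with response rate and has little power, even when response rates are equal

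*Protocol article*

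**What the plan says.** Section 2.2 of the protocol article lists as its fourth hypothesis: "Concordance between twins in a pair in terms of the response to END or RES modes of training will differ between MZ and DZ pairs". The matching analysis is at the end of section 3 (Planned statistical analysis), in the paragraph on secondary objectives. Response is dichotomised there: "Response rates for each modality can be derived as a percentage of positive responses (>0"). Concordance across modalities is then defined for one person: "Concordances can be derived as the percentage of individuals who positively respond to both exercise training modalities". For pairs, the text says only that, by analogy with the correlation analyses, "within-twin pair concordances for MZ and DZ can be derived for each exercise intervention and compared to each other". No definition of a concordant pair is given, no test is named, and no allowance for the response rate is stated.

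For the primary objective, the same section plans a comparison of the same twin contrast on the continuous changes: "Differences between intraclass correlations (rMZ vs rDZ) will be assessed using the likelihood-ratio test in STATA".

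Table 1 in section 2.3 gives the enrolled numbers: MZ "n = 62 (31 twin pairs, 18 F, 13 M") and DZ "n = 28 (14 twin pairs, 10 F, 4 M").

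**The concern.** Hypothesis 4 asks whether MZ co-twins are more alike in their training response than DZ co-twins. A percentage of concordant pairs does not isolate that. If twins did not resemble each other at all, the share of pairs with both positive would be the square of the response rate: 0.80² = 64% at a rate of 80% and 0.60² = 36% at 60%. Two zygosity groups that differ only in how many people respond would therefore show different concordances, and the difference could be taken for a genetic effect.

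The opposite error is also possible. Cutting a continuous change at zero discards most of the information about resemblance, so a real difference could easily be missed. The concordance result could then appear to contradict the rMZ v rDZ analysis of the same data.

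**Working it through.** **Inputs from the article.** 31 MZ and 14 DZ pairs (Table 1), assuming that all enrolled pairs are analysed; alpha 0.05 (section 3); planning correlations 0.80/0.30 and earlier FMD response correlations 0.74/0.37 (section 3.2).

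**Assumptions.** A bivariate normal liability with the threshold set by the response rate. Response rates of 50–90%: the Introduction says up to 30% may not benefit, which suggests about 70% responders, but no rates by zygosity are given. A two-sided pooled two-proportion z-test, evaluated by exact binomial enumeration, because no test is named.

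**The article's own figure.** Section 3.2 gives 23 per group for "predicted correlations for rMZ = 0.80 and rDZ = 0.30, assuming alpha = 0.05" at 80% power. With Fisher's z, n = 2[(z_α + z_power)/(atanh 0.80 − atanh 0.30)]² + 3. One-sided: 2[(1.645 + 0.842)/(1.0986 − 0.3095)]² + 3 = 22.9, so 23. Two-sided: 28.2, so 29. The figure is therefore reproduced one-sided, and n in this formula counts pairs. It concerns correlations. No power is stated for concordance.

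**Step 1: dependence on response rate.** Let p be the response rate, r the liability correlation and Φ₂ the bivariate normal distribution function. Then P(both positive) = Φ₂(z_p, z_p; r), and P(same status) = 1 − 2[p − P(both positive)]. At a fixed r = 0.5:

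| Response rate | Both positive | Same status |
|---|---|---|
| 50% | 0.33 | 0.67 |
| 60% | 0.44 | 0.68 |
| 70% | 0.56 | 0.71 |
| 80% | 0.69 | 0.77 |
| 90% | 0.83 | 0.87 |

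Resemblance is identical in every row. The percentage moves with the rate under both definitions, far more so under both positive.

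**Step 2: rejection when resemblance is equal (r = 0.3 to 0.5).**

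| MZ v DZ response rate | Both positive | Same status |
|---|---|---|
| 70% v 70% | about 5% | about 5% |
| 75% v 65% | 13–14% | 7–8% |
| 80% v 60% | 38–40% | 12–14% |

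As an example, at r = 0.3 and 80% v 60% the both-positive percentages are 66.6% and 40.6%, and the test rejects in 40% of trials.

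**Step 3: power when resemblance differs and response rates are equal (50–90%).**

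| rMZ / rDZ | Both positive | Same status | Likelihood-ratio test on continuous change |
|---|---|---|---|
| 0.74 / 0.37 | 7–8% | 12–18% | about 53% |
| 0.80 / 0.30 | 8–10% | 16–30% | about 81% |

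At 0.80/0.30 and a 70% rate, the percentages to be told apart are 61.1% v 52.8% (both positive) or 82.2% v 65.6% (same status). For 80% power with equal groups this needs 557 or 109 pairs per group.

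The likelihood-ratio figures come from simulation with normal data, zygosity-specific means and equal total variances. Its rejection rate under equal correlations was 5.3–6.1%. With a stricter cut-off of 4.4 in place of 3.84, power is about 49% and 78%.

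**The case against.** A reader might infer that the comparison is invalid outright, rejecting whenever resemblance is equal. The documents do not support that. With equal response rates the error is about 5%, and a 10-point gap raises it only modestly. The article gives no response rates by zygosity. Table 1 shows that the groups differ in sex mix (13 of 31 v 4 of 14 male pairs), mean weight (74.9 v 62.6 kg) and BMI (24.4 v 21.1). That makes unequal rates plausible but does not establish a gap of any size.

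A reader might also take both-positive as the planned definition. It is stated for one individual across two modalities and is only carried over to pairs. The same-status reading is open and is affected less. A fuller plan may settle the definition and the test.

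Finally, the genetic question has its own analysis. The rMZ v rDZ test uses continuous changes, may adjust for covariates such as sex and fat-free mass, and decides whether A, C and E are estimated. Concordance enters none of it, its wording is permissive, and the planned MZ v DZ level comparisons could reveal a difference in mean response.

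All of this stands, and it limits the point to a secondary analysis. It does not remove the point. Both definitions depend on the response rate, both have low power, and hypothesis 4 is a listed hypothesis framed in terms of concordance.

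**Conclusion.** The point holds in a conditional form. The planned concordance comparison confounds resemblance with response rate whenever the MZ and DZ rates differ. The false-positive inflation depends on assumed rate gaps: slight to moderate at 10 points, and large at 20 points only under the both-positive reading.

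The loss of power does not depend on any gap. Across the assumed range of rates it is 7–30%, against roughly 53–81% for a test already in the plan. A non-significant concordance result would therefore say very little about hypothesis 4, and a significant one could not be read as a difference in resemblance without the two response rates. These figures rest on the liability model, a z-test and all 45 enrolled pairs being analysed.

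It would be wrong to conclude that the heritability results are compromised. The primary rMZ v rDZ and A/C/E analysis does not use concordance and is untouched.

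**What to change.** In the secondary-objectives paragraph of section 3, state that hypothesis 4 is tested by the planned likelihood-ratio comparison of rMZ and rDZ for the END and RES changes. Define a concordant pair, and report MZ and DZ concordance percentages descriptively only, each beside that zygosity's response rate.

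If a binary test is still wanted, compare tetrachoric correlations from a model with separate response thresholds for MZ and DZ pairs, and show their intervals.

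The cost is a change of wording, with no new data and no change to the primary analysis. The drawback of the binary option is that the tetrachoric estimate will be imprecise with 14 DZ pairs, and the interval should make this visible.

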### Washout, carryover and order effects

3.1

Analysis of the effectiveness of the washout period, carryover effects and the order effect of the exercise interventions will be assessed in SPSS and STATA. To assess the effectiveness of the washout period, the presence of carryover effects, or order effect of the exercise interventions, we will initially calculate and present summary statistics comparing groups according to the order of first administration for each intervention. The entire time series of data, including time-points following the washout, will also be presented. As a first descriptive step, group means for these comparisons will be compared using *t*-test, assuming data is normally distributed. If not, non-parametric alternatives will be used. In this way, the magnitude of change for those completing END 1st versus 2nd, and RES 1st versus 2nd, will be presented and compared. This approach will be followed by mixed models, where an ‘order’ variable (eg endurance first, endurance second) will be included in models as a factor in interactions. The length of our washout period was based on our previous findings and we do not anticipate persistent effects for the variables we will measure in this study, but any significant effects will be addressed by inclusion in our statistical models (mixed models ANOVA) of baseline values as covariates. The dependence of twins within a pair will be accounted for by fitting regression models adjusting for correlations within-twin pairs using the GEE approach in STATA to test whether time period (week 0 vs week 24) or order (END/RES vs RES/END) are associated with the outcomes.

### Sample size and power

3.2

Power analysis is based on our primary outcome measures which are highly specialized and sensitive; vascular function (FMD), cardiac and cerebrovascular adaptation. Our cardiac publications [6,8,9] have reported significant effects in fewer subjects (n = 10 and n = 13 per group) than we recruited in the present study; we observed highly significant differences utilising highly sensitive MRI. Regarding cerebral measures, previous publications and our pilot work demonstrate that cerebral blood flow is increased in older individuals (n = 9, 65–78 yrs) by 10% after intervention. Our previous twin study publications in a paediatric population [24,31] cross-sectionally revealed FMD correlations of 0.6 and 0.38 in MZ and DZ twin pairs, respectively, in a smaller sample size of 22 (11 pairs) per group [24]. In addition, this study applied an exercise intervention (8 weeks) shorter than the current study (12 weeks), and produced correlations of 0.74 and 0.37 for FMD responses in MZ and DZ groups (n = 24–6 pairs per group) [31]. A power analysis (G*Power v3.1.2), performed using the predicted correlations for rMZ = 0.80 and rDZ = 0.30, assuming alpha = 0.05, indicates that a sample size of 23 individuals in each group provides 80% power.

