In addition to the responder/non-responder phenomenon, and the question of whether low-response to one form of exercise training necessarily implies low-response to all modalities, a question relates to genetic predisposition to adaptation. Classical twin studies utilising monozygotic (MZ) and dizygotic (DZ) twin pairs have long been used to assess the contribution of unmeasured genetic and environmental effects on variation in measured traits [10,11]. Since MZ twins theoretically share 100%, and DZ twins ~50%, of their DNA [12] then a phenotype that is purely explained by genetics would hold a ratio of 2:1 consisting of correlations of 1 for MZ and 0.5 for DZ [13]. If the 2:1 ratio remains the same but the correlations are lower than these values, then both shared and unshared components may be influencing results [14,15]. In this way, classical twin studies allow researchers to stratify the total variance of a phenotype. Any excess correlation observed for MZ compared with DZ pairs is assumed to be due to the extra genetic material shared by MZ twins (under the equal environments assumption [16]), and the amount and proportion of variation in a measured trait due to additive genetic effects (A), shared environmental effects (C) and unshared effects (E) can be determined. The proportion of the total variation which is due to A is often referred to as the heritability [12,17]. Alternately, in cases where genetic and environmental effects cannot be separated, the use of a classical twin study design may make it possible to estimate the extent of familial aggregation [18].

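### The 80% power statement counts twins where the formula counts pairs, fits only an undeclared one-sided test, and rests on optimistic correlations; 14 DZ pairs fall short of its requirement

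*Protocol article*

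**What the plan says.** Section 3.2 (Sample size and power) reports one quantified power calculation, made in G*Power. It was "performed using the predicted correlations for rMZ = 0.80 and rDZ = 0.30", "assuming alpha = 0.05", and it "indicates that a sample size of 23 individuals in each group provides 80% power". Whether alpha is one-sided or two-sided is not stated.

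The same section cites the team's earlier twin work on FMD. Cross-sectional correlations were 0.6 (MZ) and 0.38 (DZ), and an exercise intervention "produced correlations of 0.74 and 0.37 for FMD responses in MZ and DZ groups".

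Table 1 (section 2.3) lists 31 MZ pairs; for DZ it gives "n = 28 (14 twin pairs, 10 F, 4 M").

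Section 3 (Planned statistical analysis) says: "Differences between intraclass correlations (rMZ vs rDZ) will be assessed using the likelihood-ratio test in STATA". The models compared have equal or different MZ and DZ covariances. A, C and E are calculated only if the difference is significant; otherwise C and E alone are reported.

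The Introduction says that a purely genetic trait "would hold a ratio of 2:1 consisting of correlations of 1 for MZ and 0.5 for DZ".

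**The concern.** A twin correlation takes one observation from each pair, so a sample size for comparing two such correlations is a number of pairs. Section 3.2 calls it individuals, although a few lines earlier it counts a previous study as 22 people in 11 pairs. The number 23 is also odd, so it cannot be a whole number of pairs.

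The unit matters because it hides a shortfall. The 28 DZ individuals in Table 1 comfortably exceed 23; the 14 DZ pairs do not.

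The sentence is the only power figure offered for the primary objective. Under section 3, a non-significant comparison removes A from the reported model and leaves all twin resemblance in C. A reader who believes that power was 80% could take that result as evidence against a genetic effect.

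**Working it through.** **Inputs.** rMZ = 0.80, rDZ = 0.30, alpha = 0.05 and 80% power (section 3.2); 31 MZ and 14 DZ pairs (Table 1); alternative correlations 0.74/0.37 and 0.60/0.38 (section 3.2). I add 0.80/0.40, the widest gap that a 2:1 ratio allows when rMZ = 0.80.

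**1. Reproducing the 23.** For two independent correlations, Fisher z gives

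n per group = 2 × [(z_alpha + z_power)/q]² + 3, with q = atanh(0.80) − atanh(0.30) = 1.0986 − 0.3095 = 0.789.

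- One-sided: 2 × [(1.645 + 0.842)/0.789]² + 3 = 22.9, so 23. Power at 23 + 23 is 80.2%.
- Two-sided: 2 × [(1.960 + 0.842)/0.789]² + 3 = 28.2, so 29. Power at 23 + 23 is 70.4%.

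Here n counts pairs of values, that is, twin pairs. The published 23 is therefore 23 pairs per group, one-sided.

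**2. The literal reading.** 23 individuals are 11.5 pairs. SE = √(2/8.5) = 0.485 and 0.789/0.485 = 1.63, giving power of 37% two-sided and 49% one-sided. Simulating the planned likelihood-ratio test with a common variance gives 55% at 11 + 11 pairs and 58–59% at 12 + 12.

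**3. DZ pairs needed alongside 31 MZ pairs.** Solve 1/28 + 1/(n − 3) = [q/(z_alpha + z_power)]².

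- One-sided: the right side is 0.1007, so n = 18.4, or 19 pairs.
- Two-sided: the right side is 0.0793, so n = 25.9, or 26 pairs.

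With 31 + 14 pairs, SE = √(1/28 + 1/11) = 0.356 and 0.789/0.356 = 2.22. Power is 60% two-sided and 72% one-sided.

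**4. Power at 31 + 14 pairs across correlations (two-sided).** The likelihood-ratio figures are simulated with normal data, no covariates and no excluded pairs.

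| rMZ/rDZ | Fisher z | Likelihood ratio, common variance | Likelihood ratio, separate variances |
|---|---|---|---|
| 0.80/0.30 | 60% | about 80% | about 70% |
| 0.80/0.40 | 47% | about 70% | not run |
| 0.74/0.37 | 35% | about 53% | about 42% |
| 0.60/0.38 | 13% | about 20% | about 15% |

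The simulated type I error at 31 + 14 pairs was about 5–6%.

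**5. The assumed effect.** A = 2(rMZ − rDZ) = 2(0.80 − 0.30) = 1.00; C = 2rDZ − rMZ = 0.60 − 0.80 = −0.20; E = 1 − 0.80 = 0.20. A negative C is inadmissible as a variance component, and the ratio 0.80/0.30 = 2.67 exceeds the 2:1 given in the Introduction. The assumed gap of 0.50 compares with 0.74 − 0.37 = 0.37 and 0.60 − 0.38 = 0.22 in the cited data.

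**6. Precision of A.** SE(A) = 2 × √[(1 − rMZ²)²/31 + (1 − rDZ²)²/14] gives 0.50, 0.47, 0.49 and 0.51 for the four rows above. The 95% half-width, 1.96 × SE, is therefore about 0.9–1.0, nearly the whole 0–1 range.

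**The case against.** The strongest defence is that Fisher z is not the planned test. Section 3 describes a likelihood-ratio test in which only the covariances differ by zygosity, and nothing there mentions separate variances. On that reading, the enrolled 31 + 14 pairs have about 80% power at 0.80/0.30, the level the article claims. This stands, and it limits the conclusion. It does not make the sentence correct, because the sentence gives a different calculation, unit and sample size, and the 80% depends on the optimistic correlations and on equal variances.

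The sidedness of the planned test is also open. Section 3 speaks of an additional MZ covariance; if it is fitted as a variance that cannot be negative, the test is one-directional. Hypothesis 4, that concordance will differ between MZ and DZ pairs, points the other way. The fault is that sidedness is not stated, not that one-sided is necessarily wrong.

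Comparing two correlations does not require the ACE model, so 0.80/0.30 is not itself an arithmetic error. It is an optimistic choice that sits badly with the model to be fitted. The rule that drops A belongs to section 3, and the Introduction already says that, where genetic and environmental effects cannot be separated, the design may only estimate familial aggregation.

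A reader might go further in three ways that the documents do not support:

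- That DZ enrolment misses the target on any reading. Taken literally, 28 individuals exceed 23; the shortfall appears only in pairs.
- That 23 DZ pairs were required. That is the equal-group figure; alongside 31 MZ pairs it is 19 or 26.
- That the sample cannot distinguish the correlations seen earlier. At 0.74/0.37 the planned test has about even odds; the power is very low only at 0.60/0.38.

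**Conclusion.** The power statement is wrong as written. Its 23 is a number of pairs and matches only an undeclared one-sided alpha of 0.05. The two-sided requirement is 29 pairs per group. The 14 DZ pairs fall short of what the same formula needs with 31 MZ pairs, whichever sidedness is chosen.

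For the analysis actually planned, the weakness lies mainly in the assumed correlations. Power is near the claimed level at 0.80/0.30 but no better than about 70% at the ACE limit for rMZ = 0.80, and 20–53% at the team's own earlier values. It is lower if variances differ by zygosity or if pairs are excluded under the 80% adherence rule in section 2.6. The likelihood-ratio figures rest on the simulation assumptions listed with the calculation. A non-significant rMZ v rDZ comparison would therefore say little about whether a genetic effect exists.

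**What to change.** Rewrite the last sentence of section 3.2 and add a few lines:

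- Keep 0.80/0.30 as the basis originally used, and label it as optimistic and outside the admissible ACE range.
- Change the unit to 23 pairs (46 twins) per group.
- State the sidedness used in that calculation and the sidedness of the planned likelihood-ratio test.
- State the enrolled numbers: 31 MZ and 14 DZ pairs.
- Give likelihood-ratio power at those numbers for 0.80/0.40, 0.74/0.37 and 0.60/0.38, saying whether a common variance is assumed.
- Give the expected 95% half-width for A (about 0.9–1.0).
- Say that a non-significant rMZ v rDZ difference is inconclusive about a genetic effect.

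The cost is one rewritten paragraph and a less favourable power statement. Intervention data collection ended in September 2019 (section 2.5), and no extra enrolment is proposed.
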